### Interventions

2.8

The comprehensive intervention measures of the trial group will be the teaching and practice of psychological comfort adjustment technology, whereas the control group will attend health education talks. In this study, blind method will be applied to the research objects, double blind fashion. All participants receive ten ninety-minute treatments over 10 weeks and once a week, divided into physical health and psychological section. Treatments are provided at no cost to participants. The contents of 10 activities in the intervention group and the control group are shown in Table 1.

**Table 1 T1:**
[figure not shown]
Details of each regimen.

### Outcomes

2.9

Primary endpoint is the psychological scale score. Secondary endpoints are blood pressure in these patients, awareness of physical and mental health, and self-management efficiency. We will measure these parameters separately in three time-points, that is, base, mid court (the fifth week), and final lines. We will evaluate the psychological scale score, blood pressure, physical and mental health awareness and self-efficacy at week 10.

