**Methods/design::**

We will conduct a prospective, double-blind, randomized, multiple-centers study. Eighty patients enrolled in this trial will be randomized at 1:1 ratio. The primary endpoint is will be the reduction of the patient psychological scale (PHQ-9) score. Secondary endpoints will be the drop in blood pressure, awareness of physical and mental health and self-efficacy scale. Measurements will be performed at baseline, 5-week (questionnaires only), 10-week (primary endpoint), using the Anxiety Screening Questionnaire (GAD-7) and Depression Scale (PHQ-9). Data analysis will be carried out using the SPSS v.25 software assuming a level of significance of 5%. Results will be analyzed using multilevel, regression analysis and hierarchical linear models.

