### Statistical analysis

2.7

The primary population for efficacy analysis is the intention-to-treat population, defined as all randomized patients. The stratified OR will be estimated by logistic regression analysis with randomized factors as covariates, and multivariate regression analysis will be used to explore interactions between therapies and back-ground factors. Linear models will be used to test for between group differences in the continuous outcome measures. Secondary endpoints are summarized using 

 and frequency. Missing data will be excluded from the analysis of the corresponding endpoint.

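### The Abstract limits week 5 to questionnaires while section 2.9 also measures blood pressure then; reconcile the two and, if the reading is kept, use it in the analysis

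*Protocol article*

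**What the plan says.** **Visit schedule.** The Abstract (Methods/design) states: "Measurements will be performed at baseline, 5-week (questionnaires only), 10-week (primary endpoint"). Section 2.9 (Outcomes) states: "Secondary endpoints are blood pressure in these patients, awareness of physical and mental health, and self-management efficiency", and directly after that: "We will measure these parameters separately in three time-points", which it gives as baseline, week 5 and the end. No parameter is exempted at the middle visit. Its last sentence adds: "We will evaluate the psychological scale score, blood pressure, physical and mental health awareness and self-efficacy at week 10".

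**Analysis.** The Abstract says: "Results will be analyzed using multilevel, regression analysis and hierarchical linear models". It does not name the levels. Section 2.7 names linear models for between-group differences in continuous outcomes, takes all randomized patients as the primary efficacy population, and says: "Missing data will be excluded from the analysis of the corresponding endpoint". Section 2.11 says that data gathered before a participant withdraws go into the analysis unless the participant asks for their removal.

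**The concern.** Blood pressure is the one listed outcome that is plainly not a questionnaire, so the Abstract's restriction bears directly on it. Under the Abstract a patient has one blood-pressure value after baseline; under 2.9 the patient has two. Staff cannot satisfy both texts, and a week-5 reading that was not taken cannot be recovered.

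At stake is the contribution of patients who leave between weeks 5 and 10. With a week-5 reading and a model that uses it, they inform the week-10 blood-pressure contrast. Without the reading they have no blood pressure after baseline, so 2.11's undertaking on data before withdrawal has nothing to act on for follow-up blood pressure.

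**Working it through.** **1. The two schedules side by side.**

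| Outcome | Abstract, week 5 | Section 2.9, week 5 | Week 10 (both) |
|---|---|---|---|
| PHQ-9 (primary) | yes | yes | yes |
| Blood pressure | no | yes | yes |

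Blood-pressure time-points per patient are 2 under the Abstract and 3 under 2.9. Section 2.5 mentions both 80 and 60 patients. With complete data:
- 80 patients: 80 × 2 = 160 records against 80 × 3 = 240.
- 60 patients: 60 × 2 = 120 records against 60 × 3 = 180.

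**2. Does other text settle it?** The last sentence of 2.9 fixes when endpoints are evaluated. It does not withdraw the preceding sentence on when they are measured. Section 2.5 gives assessors duties at baseline and at the end of the study. It is silent on week 5 altogether, including the questionnaires that both schedules require then, so it does not decide the matter.

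**3. What the week-5 reading could be worth.** The plan gives no figure to reproduce here. Inputs, all assumptions:
- m, the fraction lost after week 5: 0.10 and 0.25. Nothing in the article states a loss rate.
- r, the correlation of week-5 and week-10 blood pressure given baseline: 0.5 to 0.7.
- Large samples, equal loss in the two arms, loss ignorable given baseline and week 5, and clustering ignored.

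Variance of the week-10 contrast, relative to no loss:
- complete cases: 1/(1 − m)
- repeated-measures model with week 5: 1 + [m/(1 − m)] × (1 − r²)

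Ratio of the second to the first: (1 − m) + m(1 − r²) = 1 − m r².

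| m | r | Complete cases | With week 5 | Ratio | Reduction |
|---|---|---|---|---|---|
| 0.10 | 0.5 | 1.111 | 1.083 | 0.975 | 2.5% |
| 0.10 | 0.6 | 1.111 | 1.071 | 0.964 | 3.6% |
| 0.10 | 0.7 | 1.111 | 1.057 | 0.951 | 4.9% |
| 0.25 | 0.5 | 1.333 | 1.250 | 0.938 | 6.3% |
| 0.25 | 0.6 | 1.333 | 1.213 | 0.910 | 9.0% |
| 0.25 | 0.7 | 1.333 | 1.170 | 0.878 | 12.3% |

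**4. What produces the gain.** Under 2.7's rule, a week-10 linear model drops a patient without a week-10 value whether or not a week-5 reading exists. The reduction therefore needs both the reading and the change of model.

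**The case against.** The strongest reply is that little depends on this visit. Section 2.9 evaluates blood pressure at week 10, section 2.7 names only linear models for continuous outcomes, and PHQ-9 is collected at week 5 on either reading. All of that stands and limits the point to a secondary endpoint at an intermediate visit.

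Three stronger readings are tempting, and the article does not support them:
- **That the planned multilevel analysis fails without week-5 blood pressure.** The levels are not named. Section 2.10 describes groups within communities and an intragroup correlation of 0.01, so the levels may be clusters of patients. Week-5 blood pressure is needed only if time is a level.
- **That a quarter of patients will be lost after week 5.** The figures 80 and 60 in 2.5 come from a sentence on recruitment, not on attrition. The value m = 0.25 is illustrative only. Patients lost before week 5 would add no follow-up data under either schedule.
- **That sites will diverge and leave week-5 readings for a selected subset.** Staff may work from the assessment schedule in Figure 2, which is not shown. It may indicate which version is intended, so divergence in practice cannot be inferred. It would not, however, make the Abstract and 2.9 agree.

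**Conclusion.** The contradiction is real, and the two passages must be reconciled. It does not threaten the primary endpoint or a simple week-10 blood-pressure comparison. The benefit of resolving it in favour of 2.9, together with a suitable model, is modest: a variance reduction of m × r², about 2.5% to 5% at 10% loss and 6% to 12% at 25% loss, on assumed loss rates and correlations. That is the value of an inexpensive improvement, not the cost of the inconsistency by itself. It is worth making because the reading is already in 2.9 and because it lets the blood-pressure analysis honour 2.11.

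**What to change.** Keep the 2.9 schedule, delete the Abstract's restriction of week 5 to questionnaires, and check that Figure 2 agrees. Replace complete-case exclusion for blood pressure with a repeated-measures linear model: week-5 and week-10 values as outcomes, baseline blood pressure as covariate, and the between-group contrast at week 10 as the result reported. Patients who lack only the week-10 value then stay in the analysis.

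If week 5 is to remain for questionnaires, 2.9 must exempt blood pressure at that visit, and the analysis should be a baseline-adjusted comparison at week 10.

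The cost is wording and a model specification, plus at most one blood-pressure reading at a weekly session that participants already attend (section 2.8).

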### Sample size calculation

2.10

The sample size will be calculated by PASS software based on the difference test formula for 2 samples mean comparison in group randomized controlled trial. The indicators will be selected as follows:

(1)The error setting is 1−*β *=* *0.9, *α *=* *0.05.(2)Sample size setting: There are two groups for each community in the intervention group and the control group, with about 30 people in each group. The number of communities in the intervention group and the control group is same.(3)Effect scale setting: there is no change in the control group after the intervention, and the mean change is calculated based on the anxiety end-line and baseline difference of the intervention group in the pretest hypertension patients. Intragroup correlation was set to 0.01.

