### Enrollment, randomization and blinding

2.5

We plan to recruit 80 cases and actually 60 people; patients will be randomized at 1:1 ratio in the Gansu Gem Flower Hospital. The study participants do not know their grouping, the outcome assessors and the analyst do not know the grouping of the research objects, are responsible for collecting the baseline data, the physical examination, questionnaire survey at the end of the study, and conducted data entry and statistical analysis. The blinding codes will place in a sealed envelope and will be revealed only when adverse events occur or at the terminal analysis.

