### Limitations of this study

2.14

Intrinsic and extrinsic factors influencing physical and mental health factors are diverse, therefore, the relative importance of circumstances may vary with time and this needs to be considered when designing the programs and policy interventions.

The current study will be performed in 3 areas of Lanzhou, which doesn’t necessarily reflect the entire country, the possible treatment bias may not be excluded completely.

Moreover, we realize that the intervention implementation process, team training, different times, resources and adaptations, may have some impacts to the outcomes of the study.

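### The sample size assumes randomised groups, section 2.5 randomises patients, and the section 2.7 models name no group term although the Abstract promises multilevel ones

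*Protocol article*

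**What the plan says.** The protocol article describes the unit of allocation in two ways.

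- **Section 2.10 (Sample size calculation)** uses PASS and the "difference test formula for 2 samples mean comparison in group randomized controlled trial". It sets power 0.9, alpha 0.05, about 30 people per group and an intragroup correlation of 0.01. It adds: "The number of communities in the intervention group and the control group is same".
- **Section 2.5 (Enrollment, randomization and blinding)** says that "patients will be randomized at 1:1 ratio in the Gansu Gem Flower Hospital". The Abstract also randomises patients 1:1. Neither describes allocation of communities or groups.

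It also describes the analysis in two ways.

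- **Section 2.7 (Statistical analysis)**: "Linear models will be used to test for between group differences in the continuous outcome measures". No group, session or community term is named.
- **Abstract, Methods/design**: "Results will be analyzed using multilevel, regression analysis and hierarchical linear models".

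The Abstract plans 80 patients. Section 2.5 plans 80 but gives 60 as the actual number. Section 2.10 itself gives no resulting N, no number of communities, no SD and no numerical effect. Section 2.14 (Limitations) says: "The current study will be performed in 3 areas of Lanzhou".

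**The concern.** The unit of randomisation decides which test is valid, how many degrees of freedom it has, and which sample size formula applies. Here sizing follows one unit and allocation another, and the two statements of the analysis differ on whether a group level is modelled at all.

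Two things are at stake. First, the sponsor itself judged that outcomes within a group are correlated, since it set a non-zero intragroup correlation. If the section 2.7 model is then run as though patients were independent, standard errors are too small and the test rejects too often. This can happen even when patients are randomised, if each arm is taught in its own groups. Second, if whole groups or communities are allocated, the number of groups per arm limits the test more than the number of patients does. With one group per arm, the arm effect cannot be separated from the group effect. That cannot be repaired after enrolment.

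**Working it through.** **Inputs from the protocol article.** Alpha 0.05, power 0.9, intragroup correlation (ICC) 0.01 and group size of about 30 (section 2.10); N = 80 (Abstract, section 2.5) or 60 (section 2.5); 3 areas (section 2.14). **Assumptions.** The test is two-sided, which is not stated. A layout of 80 people as four groups of 20 is also an assumption, used to show a smaller group size.

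**1. Can the 90% power be reproduced?** No. It needs a mean difference, an SD and the number of groups. The effect is described only in words, as a change in anxiety seen in a pretest. What can be solved is the standardised difference d detectable at 90% power, by the normal approximation d = (1.960 + 1.282) × √(2 × DE / n per arm), where DE is the design effect:

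| N | Layout | DE | d |
|---|---|---|---|
| 80 | independent patients | 1 | 0.725 |
| 60 | independent patients | 1 | 0.837 |
| 80 | four groups of 20 | 1.19 | 0.791 |
| 60 | two groups of 30 | 1.29 | 0.951 |

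The last row shows the approximation only. Step 4 explains why that layout has no valid test.

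**2. Design effect.** DE = 1 + (m − 1) × ICC.
- m = 30: 1 + 29 × 0.01 = 1.29.
- m = 20: 1 + 19 × 0.01 = 1.19.

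**3. True error of a nominal 5% test that ignores groups.** Error = 2 × (1 − Φ(1.96/√DE)).
- m = 30: 1.96/√1.29 = 1.726, error 8.4%.
- m = 20: 1.96/√1.19 = 1.797, error 7.2%.

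Simulation with 100,000 trials per setting gave 8.4% (60 people, one group of 30 per arm), 8.6% (120 people, two groups of 30 per arm) and 7.1% (80 people, two groups of 20 per arm).

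Conversely, a d that gives 90% power for independent patients gives about 84% (DE 1.19) or 81% (DE 1.29) once the variance is corrected, by the normal approximation.

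**4. If whole groups are allocated.** A group-level t-test with k groups per arm has 2k − 2 degrees of freedom.
- 60 people in groups of 30: k = 1, 0 df, no valid test.
- 80 people as four groups of 20: k = 2, 2 df, detectable d at 90% power about 1.66, against 0.725 for independent patients.

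**5. Does section 2.10 lead to 80?** With groups of 30, one per arm gives 2 × 30 = 60; two per arm gives 4 × 30 = 120; one per arm in each of 3 areas gives 6 × 30 = 180. None gives 80.

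**6. Effect of a corrected model on the interval, four groups of 20.** For independent patients, SE = √(2/40) = 0.224 SD and the critical t is 1.99, so the half-width is 0.445 SD. With groups, SE = √(2 × 1.19/40) = 0.244 SD and the critical t on 2 df is 4.30, so the half-width is 1.05 SD. The ratio is 1.05/0.445, about 2.4.

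**The case against.** The strongest reply is that the Abstract already names multilevel and hierarchical linear models. A hierarchical linear model is a linear model, and a condensed article may leave its random terms to a full protocol or analysis plan that is not shown. This stands against one tempting inference: that the trial's 5% test is too liberal as a matter of fact. The documents support only a conditional statement. If the groups are in the model, the inflation does not follow from the text.

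Other stronger readings also fail.

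- *The power statement fits neither design.* Not shown. The formula, ICC and group size belong to a group-randomised design, and the same design effect can serve patient randomisation with group-taught sessions. With no effect size or SD, 90% can be neither confirmed nor refuted.
- *Three areas cannot be split equally between arms.* Nothing equates an area with a community. Section 2.10 can also be read as placing one intervention group and one control group in each community.
- *Both arms are certainly taught in groups.* Sections 2.8, 2.10 and 3 make this plausible, but Table 1 is not shown, and the number and size of session groups are not given.
- *The error is far above 8%.* An assumed ICC of 0.05 would give 16.1% (groups of 20) or 21.1% (groups of 30), but nothing in the protocol supports that value.

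What the reply does not remove is the conflict itself. Condensing can omit a detail, but it does not explain two different units of randomisation in sections 2.5 and 2.10, or an analysis section that names no group level when both the Abstract and the sample size assume one.

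**Conclusion.** The point holds as an internal contradiction that must be reconciled. The protocol sizes for randomised groups and randomises patients. It assumes clustering for sizing and promises multilevel models in the Abstract, yet does not carry either into section 2.7.

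The consequence is conditional. A true error of about 7.2% to 8.4% requires that the section 2.7 model omits groups, that outcomes correlate within arm-specific groups, that the ICC is the protocol's own 0.01, that groups number 20 to 30 people, and that the test is two-sided. The absence of any valid test applies only if whole groups of 30 are allocated with 60 people in total. Whether the trial has 90% power remains open under either design.

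**What to change.** State one unit of randomisation and use it in sections 2.5, 2.7 and 2.10.

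**If patients are randomised**, as section 2.5 and the Abstract say:
- remove the group-randomised formula and the sentence on the number of communities from section 2.10;
- keep the design effect 1 + (m − 1) × ICC for any sessions taught in groups;
- record each patient's session group;
- in section 2.7, make the primary PHQ-9 model the multilevel model that the Abstract promises, with session group as a random effect and small-sample degrees of freedom. Where sessions are taught in groups, this needs more than one session group per arm.

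**If communities or groups are allocated**, say so in section 2.5, state their number (more than one per arm), and analyse with the group as the unit.

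In either case, restate power and N with the effect size, SD, group size and number of groups.

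**Cost.** Changes to the wording and one extra recorded variable. Confidence intervals become wider: slightly with many small session groups, but about 2.4 times as wide with four groups and 2 df. The power statement must reflect whichever applies, and N or the number of groups may have to rise.

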#### Inclusion criteria

2.3.1

1.Hypertensive patients (systolic blood pressure > 140 mmHg, and/or diastolic blood pressure > 90 mmHg)2.Depression scale (PHQ-9) evaluation score ≥ 5 points3.Aged 18 to 69 years4.Understand the questionnaires without obvious barriers to daily communication5.Stay in the current residence within the next 6 months.

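### The sample size section assumes no change in an active, contact-matched control arm, so the 90% power is probably overstated, by an amount the article does not allow one to compute

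*Protocol article*

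**What the plan says.** **Protocol article, section 2.10 (Sample size calculation).** Power is set at 0.9 and alpha at 0.05, for a calculation "based on the difference test formula for 2 samples mean comparison in group randomized controlled trial". The effect has two parts. For controls, "there is no change in the control group after the intervention". For the treated side, "the mean change is calculated based on the anxiety end-line and baseline difference of the intervention group in the pretest hypertension patients". No numerical effect and no standard deviation are given.

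**Section 2.8 (Interventions).** The trial arm is taught psychological techniques, "whereas the control group will attend health education talks". Contact is the same in both arms: "All participants receive ten ninety-minute treatments over 10 weeks and once a week".

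**Section 2.3.1 (Inclusion criteria).** Entry requires "Depression scale (PHQ-9) evaluation score ≥ 5 points".

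**Abstract and section 2.5.** The abstract makes reduction in PHQ-9 the primary endpoint, with week 10 as the primary time point. Section 2.5 says that participants do not know their group, and gives both 80 and 60 as the number of patients.

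**The concern.** With the control change fixed at zero, the planned difference between arms equals the whole before-after change in treated pretest patients. A before-after change in one group cannot separate the effect of the intervention from the effects of time, attention, expectation and retesting.

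The trial's own design gives three reasons to expect controls to improve:

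- They receive the same number and length of sessions as the trial arm.
- They are meant not to know which arm they are in, so expectation should act in both arms.
- All patients enter because their score on the primary endpoint scale is at or above a cut. Scores selected in this way tend to fall on retest without any treatment.

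The pretest figure is also a change in anxiety, while the primary endpoint is a depression score. Even the treated half of the planning effect is therefore not shown to apply to PHQ-9.

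What is at stake is the planning claim. If controls improve, the trial has less chance than stated of detecting a real effect, and readers would weigh a non-significant result against a power figure that the design does not support.

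**Working it through.** **1. Can the plan's own figure be reproduced?** No. The known inputs are power 0.90, alpha 0.05 (sidedness not stated; two-sided assumed here), 1:1 allocation, intracluster correlation 0.01, groups of about 30, and 80 or 60 patients. The mean change and its standard deviation are missing, so no sample size can be derived or checked. One can only solve for the standardised effect d that would give 90% power at each size mentioned.

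Formula: d = (1.960 + 1.282) × √(2 × DE / n per arm), where the design effect DE = 1 + (m − 1) × 0.01. For groups of m = 30, DE = 1 + 29 × 0.01 = 1.29.

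| Patients in total | DE | d for 90% power |
|---|---|---|
| 80 | 1 | 3.242 × √(2/40) = 0.725 |
| 80 | 1.29 | 0.823 |
| 60 | 1 | 3.242 × √(2/30) = 0.837 |
| 60 | 1.29 | 0.951 |

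**2. What does control improvement do to power?** Let f be the control change as a fraction of the planned treated change. Assume that the trial arm changes exactly as planned, that the standard deviation is as planned, and that the design has exactly 90% power at f = 0. The difference between arms is then (1 − f) times the planned one. Under the normal approximation:

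power = Φ[(1 − f) × 3.242 − 1.960]

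The sample size, standard deviation and intracluster correlation cancel, so the same figures apply to 80 or 60 patients, with or without clustering.

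| f (assumed) | (1 − f) × 3.242 − 1.960 | Power |
|---|---|---|
| 0 | 1.282 | 90% |
| 0.10 | 0.957 | 83.1% |
| 0.25 | 0.471 | 68.1% |
| 0.50 | −0.339 | 36.7% |

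**3. What would restoring 90% take?** The sample size must be multiplied by 1/(1 − f)². This is 1.23, 1.78 and 4.0 for f = 0.10, 0.25 and 0.50. From 40 per arm it gives 50, 72 and 160 per arm after rounding up, or 100, 144 and 320 in total.

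**4. Which value of f applies?** The article gives none. Sections 2.8, 2.5 and 2.3.1 make a value above zero likely but do not fix it. Regression to the mean is not sized here: the article gives no source-population mean, standard deviation or retest correlation, and a figure in PHQ-9 points could not be set against an unstated change in anxiety.

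**The case against.** The strongest reply is that 90% is an input to a calculation described in the future tense, not a power claimed for a stated sample size. Nothing ties the calculation to 80 or 60 patients. A generous sample could leave adequate power even if controls improve, and the fractions 10%, 25% and 50% are arbitrary. This stands as far as size is concerned: the table is an illustration, not an estimate of this trial's power. It does not rescue the assumption. Zero control change is stated without justification for an active, contact-matched arm, and any improvement there lowers power below whatever was planned.

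Three stronger readings are tempting, and the article does not support them:

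- **That power is certainly below 90% by a known amount.** The shortfall depends on controls improving, which is likely but not quantified, and on the design sitting at exactly 90% when they do not.
- **That the pretest change contains the same regression to the mean and attention effect as the trial will.** The article does not say how the pretest patients were selected or what contact they had. Selection on PHQ-9 would also affect an anxiety score only as far as the two scales correlate. The defensible point is narrower: a change in treated patients alone is not a difference between arms.
- **That the trial's result will be biased.** Section 2.7 compares the randomised groups, so improvement common to both arms cancels. Only the planning is affected.

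**Conclusion.** The concern holds as a point about planning. Zero control change is hard to defend given matched sessions in both arms and entry by a cut on the primary endpoint scale. The difference between arms is likely to be smaller than planned, so the 90% power is probably overstated. The direction rests on controls improving at all, for which the design gives good reason.

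The size cannot be computed from the article. The figures of about 83%, 68% and 37% are conditional on three things: exactly 90% two-sided power at zero control change, a trial arm that performs as planned, and the assumed control fractions. They show how sensitive the claim is: a control response of one tenth of the planned change already costs about seven percentage points.

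The section should be revised. Nothing here invalidates the randomised comparison.

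**What to change.** In section 2.10:

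1. Delete the assumption of no control change.
2. Define the planning effect as the between-arm difference in PHQ-9 at week 10, net of expected control improvement, with its standard deviation and source. Do not use an anxiety change for this.
3. Restate power over a range of control change, for example 0%, 25% and 50% of the treated change.

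If no credible PHQ-9 planning data exist, state instead the between-arm PHQ-9 difference that the enrolled number can detect with 90% power. This first requires section 2.5 to reconcile 80 with 60. Without clustering, the detectable difference is 0.725 standard deviations at 80 patients and 0.837 at 60; with a design effect of 1.29 it is 0.823 and 0.951.

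The cost is a recalculation, some rewording and a less favourable stated power. No extra patients are needed to make the statement honest. It does not restore 90% power; if the sponsor wants that, the multipliers in the working show the order of the increase.

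### The sample size takes its effect from a change in anxiety, but the primary endpoint is the PHQ-9 depression score, so the 90% power is not shown to apply to the primary test

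*Protocol article*

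**What the plan says.** **Primary endpoint.** The Abstract (Methods/design) states: "The primary endpoint is will be the reduction of the patient psychological scale (PHQ-9) score". It marks week 10 as the primary time point. Section 2.9 is shorter and names no scale: "Primary endpoint is the psychological scale score".

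**Instruments.** The Abstract describes GAD-7 as the anxiety questionnaire and PHQ-9 as the depression scale. Both are administered.

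**Entry.** Section 2.3.1 requires "Depression scale (PHQ-9) evaluation score ≥ 5 points". No inclusion criterion sets a minimum anxiety score.

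**Sample size.** Section 2.10 gives power 0.9 and alpha 0.05 as settings. It assumes that "there is no change in the control group after the intervention", and for the intervention arm "the mean change is calculated based on the anxiety end-line and baseline difference of the intervention group in the pretest hypertension patients". It prints no mean change, SD or resulting number of patients. The numbers 80 (planned) and 60 (described as actual) appear in section 2.5, without a link to this calculation.

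**The concern.** A power figure belongs to one endpoint, through that endpoint's expected difference and SD. Here the difference comes from anxiety, and the test that decides the trial is on a depression score. In the article's own terms these are two instruments. Nothing says that a PHQ-9 change was used, or that the anxiety change stands in for it.

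The entry rule adds to the doubt. Patients are selected on PHQ-9 and not on anxiety, so the anxiety change seen in the pretest need not match the PHQ-9 change in the enrolled patients.

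At stake is the justification for the trial's size. Readers will take 0.9 as the chance of detecting the hoped-for effect on the primary endpoint, and the article gives no support for that.

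**Working it through.** **1. The plan's own figure.** The 0.9 cannot be reproduced. Section 2.10 gives neither a mean change nor an SD, for either scale. A condensed article may leave those values to the full protocol, so their absence is not the point. What can be checked is how far a power of 0.9 for one scale carries over to another.

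**2. Inputs.** Power 0.9 and alpha 0.05 come from section 2.10. The 1:1 allocation and the 80 or 60 patients (40 or 30 per arm) come from section 2.5. Assumptions made here: a two-sided test, because sidedness is not stated, and individual randomisation.

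**3. Transfer of power from anxiety to PHQ-9.** Suppose the sample size gives exactly 90% power for the anxiety effect. Its standardized effect divided by its standard error is then 1.960 + 1.282 = 3.242. If the PHQ-9 standardized effect is a fraction f of the anxiety one, then

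power = Φ(f × 3.242 − 1.960).

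| f | f × 3.242 − 1.960 | Power for PHQ-9 |
|---|---|---|
| 0.5 | −0.339 | 37% |
| 0.7 | 0.309 | 62% |
| 0.8 | 0.633 | 74% |
| 0.9 | 0.957 | 83% |
| 1.0 | 1.282 | 90% |
| 1.1 | 1.606 | 95% |

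This result does not depend on the sample size. Only f = 1 returns the stated setting.

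**4. What the stated sizes can detect.** The standardized difference detectable with 90% power is d = (1.960 + 1.282) × √(2/n).

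- n = 40 per arm: 3.242 × √(2/40) = 3.242 × 0.2236 = 0.725. The two-sample t-test gives 0.734.
- n = 30 per arm: 3.242 × √(2/30) = 3.242 × 0.2582 = 0.837. The t-test gives 0.851.

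If alpha were one-sided, the normal-approximation values would be 0.654 and 0.756.

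**5. Power under assumed PHQ-9 effects.** The documents give no PHQ-9 effect, so these are illustrations only (two-sided, normal approximation). At d = 0.5, power is 61% with 40 per arm and 49% with 30. At d = 0.8, it is 95% and 87%.

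**The case against.** Several points limit how far this goes.

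- **Anxiety and depression changes may be related.** An anxiety change may carry some information about PHQ-9, and section 2.2 describes the target patients as having both conditions. This stands. The defensible statement is that the 90% is not shown to carry over, and not that the anxiety data are uninformative.
- **A reader might infer that the trial is underpowered.** The documents do not support that. With no PHQ-9 effect or SD given, power for PHQ-9 may lie on either side of 90%.
- **A reader might take 0.9 as a claim about 80 or 60 patients.** Section 2.10 lists it as an input and reports no resulting number. Section 2.5 does not refer to it.
- **A reader might infer that either scale could be declared primary, with an inflated type I error.** Section 2.9 does leave the scale unnamed. But it reuses the term that the Abstract attaches to PHQ-9, and GAD-7 is never called an endpoint. No two-scale test is planned, so an error rate for one would describe an analysis that nobody proposes.
- **A reader might inflate the detectable differences by a design effect.** Section 2.10 does say that "Intragroup correlation was set to 0.01", with groups of about 30. Groups of that size do not fit 40 per arm, and at 30 per arm they leave one cluster in each arm, which gives no valid cluster comparison. Whether randomisation is by group or by patient is a separate matter.

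None of this removes the mismatch, and no section reconciles the two scales.

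**Conclusion.** The concern holds as an internal contradiction: the sample-size effect is an anxiety change and the named primary endpoint is a depression score. The power setting of 0.9 is therefore unsupported for the primary test. Its possible size is the range in the working: about 74% if the PHQ-9 standardized effect is 80% of the anxiety one, and about 95% if it is 110%. This assumes exactly 90% power for anxiety and a two-sided 5% test.

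That PHQ-9 is the primary scale rests on the Abstract, supported by the PHQ-9 entry criterion. If GAD-7 was in fact intended, the Abstract would be the part in error. On either reading the Abstract and section 2.10 do not agree and must be reconciled.

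**What to change.** **Section 2.9:** name the week-10 PHQ-9 score as the single primary endpoint, in line with the Abstract, and state that GAD-7 is not primary.

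**Section 2.10:** replace the anxiety-based effect with the expected between-arm PHQ-9 difference and its SD, and restate the calculation on that basis.

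**If there are no PHQ-9 pilot data:** replace the 90% setting with the difference detectable at the fixed sample size. Under individual randomisation, two-sided 5% and 90% power, this is about 0.73 SD at 40 per arm or 0.85 SD at 30 per arm, whichever number the sponsor confirms.

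**Cost:** wording and a short recalculation. The stated power may become less favourable. No extra patients are needed if the detectable difference is reported at the fixed size; a full recalculation from a PHQ-9 effect could change the number required.
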